### Verbal descriptor scale

Verbal descriptor scale will be used to assess different levels of pain intensity, which has good reliability and validity in elderly patients [29].

### Quality of Life Short Form-36 (SF-36)

SF-36 is a well-validated functional status questionnaire to measure health-related quality of life in eight domains, including physical functioning, health perception, etc. A higher score indicates better function [17].

### Quadriceps muscle strength

Quadriceps muscle strength will be measured on the affected limb with an isometric dynamometer (Baseline, Genova, Italy). Subject will sit on a chair with both feet above ground, while raising the affected leg 45° forwards. The dynamometer will be placed above the ankle and the subject will push the leg forward with maximum force (N). Measurements will be repeated three times and the maximum value will be used for evaluation [17].

### Balancing ability

To assess balancing ability, the Biodex Balance System SD (Biodex Medical Systems Inc., Shirley, NY, USA) is used to measure the static and dynamic ability of patients to maintain center of balance. The score generated by the machine assesses the deviation from the center via an Overall Stability Index (OSI), Anterior/Posterior Stability Index (APSI), and Medial/Lateral Stability Index (MLSI), which have been shown to be reliable tools for objective assessment of postural stability in several studies in elderly patients [22].

### Times Up and Go (TUG) test

The TUG test will be used to test basic mobility skills, which is a useful predictor of risk of falls. The patient will stand from a chair, walk 3 m, and travel back and sit back on the chair. The time in seconds (s) is recorded [22].

### Falls

Mortality will be measured at 1 month, 3 months, and 1 year via a fall calendar, which is well established in clinical trials for elderly patients [17].

### Mortality

Mortality will be measured at 1 month, 3 months, and 6 months [30]. Mortality is documented from the Clinical Management System (CMS) from Hospital Authority, a central public computerized system for patients in Hong Kong [23].

### Compliance assessment

A smart card is also given to each participant to record compliance to placebo and LMHFV [17].

### Adverse event handling

Currently, there is no report of adverse event in the use of LMHFV. In case of unusual conditions including intolerable pain, LMHFV treatment will be terminated and clinicians will follow-up the patient. Any adverse events or problems during the study will be verified and documented by independent staff members.

### Data collection, monitoring, and management

The research assistant will be trained to ensure accuracy of outcome assessments and data collection. The ethics committee will oversee and audit any issues raised and corresponding measures will be taken if necessary. Subjects not willing to continue can withdraw at any time. The study will comply with the good clinical practice guidelines. Each patient will be assigned an identification code. The patient identification code list and database will be safeguarded.

### Statistics

All results will be expressed in mean ± standard deviation. Statistical analysis will be performed using SPSS (IBM, NY, USA). One-way (for between-group differences in over-time changes), two-way (for interaction effect among time and group), and group repeated measures ANOVA with post-hoc Bonferroni analysis, as well as independent/paired *t* tests will be performed. Significance level is set at *p* < 0.05 (2-tailed).

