**Methods:**

This is a randomized, double-blinded, placebo-controlled clinical trial to evaluate the effect of LMHFV in accelerating trochanteric hip fracture healing. All fractures undergo cephalomedullary nail fixation. The primary outcome of this study is time to fracture healing by X-ray. Computed tomography (CT) and dual-energy X-ray absorptiometry (DXA) will also be performed. Blood circulation at the fracture site will be assessed by dynamic perfusion magnetic resonance (MR). Clinical results include functional recovery by muscle strength, timed up and go test (TUG), quality of life questionnaire (SF-36), balancing, falls, and mortality.

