### Sample size

In this study, time to radiologic healing is the primary objective. This is a well-accepted quantitative approach to evaluate fracture union, as in our previous study [21]. We expect 20% acceleration of radiologic healing time (our animal data confirms 30% acceleration [9]). A sample size of 100 will detect a significant difference using ANOVA with 80% power and 0.05 significance level (PASS 11.0, NCSS, LLC, Utah, USA). Our previous clinical trial [17] confirmed that compliance of vibration treatment was very good with normal subjects at 66% on average [17]. We conservatively increase the sample size to 120, assuming 15% dropout rate.

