### Interventions

Patients will be randomly allocated to placebo or vibration group [22]. Vibration is treated with LMHFV (V-health Ltd, Hong Kong) at 35 Hz, 0.3 g (*g* = gravitational acceleration) for 20 min/day, 5 times/week [17], while the placebo group will have sham treatment to stand on the LMHFV platform for 20 min/day, 5 times/week. Sound emitted by machine masks the noise an active machine makes [24]. Treatment is started at 3 days post-operation for a total of 14 days (protocol change from 6 months due to COVID-19 for patient feasibility). Patients will be followed up to 6 months.

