## Outcome assessments

### Plain radiographs

Anteroposterior and lateral X-ray (DRX-Evolution, Carestream Health, Rochester, NY, USA) of fracture site will be performed at baseline, 6, 12, and 26 weeks post-operation. Films will be assessed by two blinded surgeons independently, to note healing in the AP or lateral film [21]. Fracture healing is defined based on the Radiographic Union Score of Hip (RUSH), which assesses callus formation and visibility of fracture line at 4 cortices [25].

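### Time to healing can only be recorded as 6, 12 or 26 weeks and is undefined for unhealed patients, yet it is powered by ANOVA and summarised as a mean ± SD

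*Protocol article*

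**What the plan says.** The abstract's Methods paragraph states: "The primary outcome of this study is time to fracture healing by X-ray". The Sample size section agrees ("time to radiologic healing is the primary objective") and attaches a method to that outcome: "A sample size of 100 will detect a significant difference using ANOVA with 80% power and 0.05 significance level". The target is a healing time 20% shorter. No control mean or SD is given.

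Under Plain radiographs, X-rays "of fracture site will be performed at baseline, 6, 12, and 26 weeks post-operation". Healing is judged on those films by the RUSH score. Under Interventions, "Patients will be followed up to 6 months".

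Under Statistics, "All results will be expressed in mean ± standard deviation". The methods listed there are one-way and two-way ANOVA and "group repeated measures ANOVA with post-hoc Bonferroni analysis, as well as independent/paired" t tests. No time-to-event, interval-censored or ordinal method is named anywhere in the article.

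**The concern.** A mean ± SD, an ANOVA and a t test each need one exact number per patient. This outcome does not supply one, for two reasons.

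- **Coarse dating.** Healing is seen only at a visit, and the gaps between films are 6, 6 and 14 weeks. The recorded time is the first visit at or after true healing, so it is almost always late, by up to 14 weeks.
- **No value for some patients.** A patient unhealed at 26 weeks, or dead before a film shows healing, has no healing time. Either the patient is left out or a number has to be invented.

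At stake are the healing times the trial will report and, if healing is slow, its ability to detect the acceleration it was designed to show. The protocol has named a method and sized the trial on it, so this is a stated choice that does not fit the data. It is not a detail left to an analysis plan.

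**Working it through.** **1. The plan's own figure.** For two equal arms (1:1 assumed), with the effect as a fraction of the control mean, n per arm = 2 × (1.96 + 0.84)² × (CV / 0.20)². No SD is stated, so N = 100 can be neither reproduced nor refuted. Solving backwards with 50 per arm gives CV = 0.357, or 0.353 with the exact t distribution. The dropout step is sound: 100 / 0.85 = 118, and 120 × 0.85 = 102, or 51 per arm.

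**2. What three reading dates do to a 20% shift.**

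| True control v treated (weeks) | True difference | Recorded | Recorded difference |
|---|---|---|---|
| 10 v 8 | 2 | 12 v 12 | 0 |
| 14 v 11.2 | 2.8 | 26 v 12 | 14 |
| 16 v 12.8 | 3.2 | 26 v 26 | 0 |

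For a single pair of times the error goes in either direction. CT at 6 and 12 weeks adds no new dates.

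**3. Recorded means at a control mean of 12 weeks.** Assume log-normal times with CV 0.354 in both arms and a treated mean of 0.8 × 12 = 9.6. The log-scale SD is √ln(1 + 0.354²) = 0.344.

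- Control: 3.2% are first seen healed at 6 weeks, 53.6% at 12, 42.4% at 26, and 0.8% are unhealed. Mean = (0.032 × 6 + 0.536 × 12 + 0.424 × 26) / 0.992 = 17.8.
- Treated: 11.6%, 67.8%, 20.5% and 0.1%. Mean = (0.116 × 6 + 0.678 × 12 + 0.205 × 26) / 0.999 = 14.2.

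Both means are about 5 to 6 weeks too long (17.8 − 12.0 = 5.8; 14.2 − 9.6 = 4.6). The ratio survives: 1 − 14.2 / 17.8 = 20%.

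**4. Power by simulation.** Same assumptions, 51 per arm, two-sided 0.05, no deaths.

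| Control mean (weeks) | Unhealed at 26 weeks, control v treated | t test, unhealed omitted | t test, unhealed scored 26 | Grouped log-rank, same films |
|---|---|---|---|---|
| 12 | 0.8% v 0.1% | about 0.75 | about 0.76 | about 0.78 |
| 18 | 11% v 3% | 0.57 | 0.65 | about 0.76 |
| 22 | 26% v 10% | 0.33 | 0.47 | about 0.77 |

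With unhealed patients omitted, the recorded acceleration falls to 11.8% at 18 weeks and 6.5% at 22 weeks, against a true 20%. A t test on exact healing dates would have power of about 0.88, but no analysis of these films can reach that.

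**5. Deaths.** Background cites 1-year mortality of 20% and 30%. At a constant hazard, the share dead by 26 weeks is 1 − √0.80 = 10.6% to 1 − √0.70 = 16.3%, or about 13 to 20 of 120 patients. Only those who die before healing is seen lack a value.

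**The case against.** **The handling of unhealed patients is not written.** One might infer that the plan drops them from the mean. No section says so: the drop-out criteria are refusal, default from follow-up and unsafe treatment, and an unseen analysis plan may set a rule. This stands, so the omission figures are conditional. The loss does not rest on omission alone, though, since scoring these patients at 26 weeks still leaves only 0.65 and 0.47. A later score would recover power (at an arbitrary 39 weeks, about 0.78 and 0.77), but the result would then depend on an invented number.

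**The control mean is unknown.** This also stands. At 12 weeks under 1% are unhealed, the recorded ratio is still about 20%, and the gain from a better method is a few points. It would therefore be wrong to infer that the stated test can never estimate the acceleration.

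**Coarse dates alone do not invalidate a comparison.** Both arms share one film schedule and blinded readers, so a test of no difference remains valid if missing values are balanced under the null. Nor does an effect of 2.4 weeks (20% of 12), being shorter than the visit gaps, become undetectable: simulated power there is about 0.75. The fault is the mismatch between outcome and method, not the schedule.

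**An analysis plan could settle it.** It could add a rule for unhealed patients. It could not turn three visit dates into a continuous, fully observed time without replacing the method the protocol names.

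**Conclusion.** The point holds as a mismatch between the primary outcome and the method fixed for it. Whatever the healing speed, mean healing times computed from first-healed visits will be too long, and some patients may have no value. Loss of effect and power is conditional: severe if control healing averages about 18 to 22 weeks, small at 10 to 12 weeks.

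The sizes rest on log-normal times, a CV of about 0.354 inferred from N = 100, 1:1 allocation, 51 per arm, and a stated assumption for unhealed patients. None of these is in the protocol except the 20% target and the totals of 100 and 120. The documents do not support saying that the plan excludes unhealed patients, that the test is invalid, or that power will be 0.33. Because this is the primary analysis, and choosing how to treat unhealed patients after unblinding invites bias, it should be corrected beforehand.

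**What to change.** For the primary outcome, replace ANOVA/t test and mean ± SD with one prespecified interval-censored or discrete-time (grouped) time-to-event analysis by randomised group:

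- Place healing between the last unhealed and the first healed film.
- Censor patients unhealed or lost at their last film.
- Report the chosen model's effect estimate with its 95% CI, and the percentage healed at 6, 12 and 26 weeks in each group.
- Treat death before healing as a competing event in the healed-percentage estimates or in a sensitivity analysis, and state which estimate is primary.

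Restate the sample-size basis for that method, giving the assumed control healing distribution and the resulting power, since the present N is tied to ANOVA.

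The cost is rewritten statistics and sample-size text, a different software routine, and a stated power that may be slightly less favourable than 80%. No new visits or patients are needed.

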### Functional and quality of life outcomes

At baseline, 2, 6, 12, and 26 weeks post-operation, all patients will be assessed with the following functional tests:

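### The Statistics section fixes mean ± SD and tests of continuous means for every result: these do not suit mortality or ordinal pain, and for repeated measures no single baseline-adjusted between-group analysis is named

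*Protocol article*

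**What the plan says.** The Statistics section of the protocol article opens with a rule that has no exception: "All results will be expressed in mean ± standard deviation". It then lists the tests: "One-way (for between-group differences in over-time changes), two-way (for interaction effect among time and group), and group repeated measures ANOVA". The same sentence adds Bonferroni comparisons after the ANOVA, and t tests of both the independent and the paired kind. The software is SPSS, with no procedure named, and the level is two-sided 0.05. The list is general. It does not separate primary from secondary outcomes and links no test to an outcome.

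The outcomes it has to serve differ in kind:

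- Functional and quality of life tests are taken "At baseline, 2, 6, 12, and 26 weeks post-operation", so each patient has up to five values.
- Densitometry is taken at four of those times (baseline, 6, 12 and 26 weeks).
- On pain: "Verbal descriptor scale will be used to assess different levels of pain intensity". This gives ordered categories.
- Mortality is recorded as dead or alive at 1, 3 and 6 months.

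**The concern.** The section does not leave the methods open for a later analysis plan. It states which will be used, and none of them is for binary, ordinal or time-to-event data.

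For the repeated continuous outcomes, several tests that could each be applied to the same data stand side by side, and none is named as the one that decides. The finding could then depend on which test is chosen after the data are seen. One listed test, the paired t test, does not compare the arms at all. Hip-fracture patients can be expected to recover over 26 weeks in either arm, so a significant within-arm change could be taken for a treatment effect. Other listed tests give up precision or patients that a single standard model would keep.

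**Working it through.** The plan gives no figure of its own for these analyses. Its nearest figure is the sample size: 100/(1 − 0.15) = 118, in line with the stated 120. The within-patient correlation ρ and the missed-visit rate are not in the documents, so both are assumptions and are shown over a range.

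**Mortality.** Background cites one-year mortality of 20% (US) and 30% (UK). With a constant hazard (assumption), the share dead by 26 weeks is 1 − 0.80^0.5 = 10.6% to 1 − 0.70^0.5 = 16.3%, or about 13 to 20 of 120. For a 0/1 variable the SD is √(p(1 − p)), so the prescribed summary would read 0.11 ± 0.31 to 0.16 ± 0.37. The SD is fixed by the proportion and tells the reader nothing more. Time of death is not used.

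**Pain.** The mean of a verbal descriptor scale depends on the numbers given to the words, and the protocol gives no reason to treat the steps as equal.

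**Paired t tests.** Suppose both arms truly change by the same amount and each paired test has power p. The chance that exactly one arm is significant is 2p(1 − p):

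- p = 0.5: 0.50
- p = 0.8: 0.32

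So one arm alone is significant in a third to a half of such trials, with no treatment effect.

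**One-way ANOVA on change.** With equal variance σ² at both times, change has variance 2σ²(1 − ρ) and the baseline-adjusted value has σ²(1 − ρ²). The ratio is 2/(1 + ρ):

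- ρ = 0.3: 1.54
- ρ = 0.5: 1.33
- ρ = 0.6: 1.25
- ρ = 0.7: 1.18

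**Two-way time-by-group ANOVA, if it has no patient term.** Assume equal correlation between all visits. A time-by-group contrast has true variance proportional to 1 − ρ, while the model uses 1. The standard error is too large by 1/√(1 − ρ):

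- ρ = 0.3: 1.20
- ρ = 0.5: 1.41
- ρ = 0.6: 1.58
- ρ = 0.7: 1.83

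In a simulation under the null (2 × 50 patients, five visits, 4,000 runs per setting) the interaction test rejected in 0.9%, 0.2% and 0.0% of runs at ρ = 0.3, 0.5 and 0.7, against a nominal 5%. Repeated-measures ANOVA on the same complete data rejected in 5.0%, 5.4% and 4.7%. For a single contrast at ρ = 0.6, a correct test with 80% power would fall to about Φ(2.80 − 1.96 × 1.58) = Φ(−0.30) = 38%.

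A group effect averaged over the five visits goes the other way. Its true variance is 1 + 4ρ times the model's, which is 3.4 at ρ = 0.6. The type I error would be 2(1 − Φ(1.96/√3.4)) = 29%, and 19% to 31% for ρ = 0.3 to 0.7.

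**Repeated-measures ANOVA, if run on complete cases.** With four visits after baseline and a share m missed at each, the share complete is (1 − m)^4. At m = 5% it is 0.95^4 = 0.815, or 98 of 120. If the planned 15% dropout is taken off first, it is 0.85 × 0.815 = 0.692, or 83 of 120. Without and with the 15%, m = 3% leaves 106 and 90, and m = 10% leaves 79 and 67.

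**The case against.** The best defence is that this is one general sentence in a condensed article, and that matching tests to outcomes and handling missing data are ordinary content of an analysis plan. That is fair, and silence on missing data is not held against the protocol here. It does not rescue a rule that covers all results and names only methods for continuous means.

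Several stronger readings are tempting, and the documents do not support them:

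- **A 29% false-positive rate.** This belongs to a group effect pooled over visits in a model without a patient term. The protocol gives the two-way ANOVA one use, the time-by-group interaction, where the same omission is conservative. The omission is itself only a reading: the sentence may mean a two-way repeated-measures model, although the two are listed apart.
- **Every test applied to every secondary outcome.** The section does not say so. It also lists independent t tests, which do compare the arms.
- **Patients with a missed visit will be dropped.** No missing-data rule is stated. Complete-case use is the habit of classical repeated-measures ANOVA. It does not apply to change scores or to t tests at one visit. The missed-visit rates above are assumptions.
- **Paired tests as declared efficacy tests.** The protocol gives them no such role.
- **Many patients cannot give a baseline functional value so soon after surgery.** The documents do not say this. The functional baseline is not dated, and chairbound or bedbound patients are excluded.

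ANOVA on change is also not an error. Under randomization it gives a valid comparison. The loss is one of precision.

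**Conclusion.** The point holds in a limited form. Three parts rest on the text alone: the stated summary and tests do not suit mortality or ordinal pain, no between-group analysis is named as deciding for the repeated continuous outcomes, and paired t tests cannot show a vibration effect.

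The loss of precision from change scores follows from a stated method. Its size, 25% to 33% more variance, rests on an assumed correlation of 0.6 to 0.5.

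Two parts are conditional. If the two-way ANOVA lacks a patient term, its interaction test has a standard error about 1.6 times too large (ρ = 0.6 assumed) and loses power. If repeated-measures ANOVA is run on complete cases, patients who miss a visit or die are lost, and the number depends on missed-visit rates that the documents do not give.

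A reader might infer that the planned error rates are badly inflated. The documents do not support that for the use they name. The label is a free improvement.

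**What to change.** Rewrite the Statistics section so that each outcome has one named between-group analysis.

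- **Repeated continuous outcomes:** a mixed model for repeated measures on all available data, with arm, visit, arm × visit and baseline. State in advance the visit whose arm difference decides.
- **Two-way ANOVA:** delete it as a separate analysis, since the arm × visit term does its work.
- **Paired t tests:** do not use them as evidence of efficacy. Within-arm change may be described.
- **Mortality:** counts by arm with a risk difference, or Kaplan-Meier estimates.
- **Pain:** category counts by visit and an ordinal (proportional-odds) model.
- **Summary rule:** limit mean and SD to continuous outcomes.

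The cost is wording only. The data are already to be collected, and the analyses can be run in SPSS, the software already named. The change should be dated before unblinding.

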### Dissemination plans

We will disseminate the trial results to healthcare professionals, the public, and other relevant groups as soon as results are available (Appendix).

## Discussion

This is the first double-blinded, placebo-controlled trial to investigate the efficacy of LMHFV in accelerating trochanteric hip fracture healing. With the current aging population and increasing number of hip fractures, strategies to enhance healing and functional recovery are crucial. LMHFV is a non-invasive treatment, which is easily acceptable for elderlies and has proven benefits for physical function in a previously conducted randomized controlled trial of 710 healthy, active, and independent postmenopausal women [17]. Benefits of LMHFV for balancing ability, muscle strength, and risk of falling were retained 1 year after cessation of the treatment [18]. No serious side effects were noted. Numerous animal studies have also shown LMHFV to significantly improve normal and osteoporotic fracture healing with increased callus formation, angiogenesis, and mineralization [6, 7, 9, 10]. However, clinical translation in hip fractures remains to be proven.

Current Fracture Liaison Services (FLS) aims to close the osteoporosis care gap and prevent secondary fractures that can lead to high morbidity and mortality [20]. However, the presence of sarcopenia often co-exists with osteoporosis leading to the geriatric syndrome “osteosarcopenia” [31]. The prevalence of sarcopenia also reaches up to 95% in males and 64% in females in osteoporotic fracture patients [32]. It has been postulated that most patients develop muscle deterioration during immobilization from a fracture. Therefore, the incorporation of effective strategies to accelerate fracture healing for early pain-free mobilization has been advocated.

The risk of an imminent fracture is also high after an initial osteoporotic fracture. In fact, more than 50% of secondary fractures occur during the first 2 years [33]. Therefore, this window of opportunity is also a golden period for intervention. Positive results of LMHFV in enhancing fracture healing and functional outcome would have a significant impact for hip fracture patients by decreasing disability. More importantly, the incorporation of LMHFV into FLS can potentially lead to a significant decrease in health care costs.

Enrolment in this trial is planned to begin in January 2021. Completion is expected to take 24 months. We speculate that positive results would allow the incorporation of LMHFV into hip fracture multidisciplinary rehabilitation programs.

The completion of the trial is expected to take 24 months.

